# Comparative effectiveness of cognitive and dynamic therapies for major depressive disorder in a community mental health setting: study protocol for a randomized non-inferiority trial

**DOI:** 10.1186/s40359-014-0047-y

**Published:** 2014-11-11

**Keywords:** Dynamic therapy, Cognitive therapy, Non-inferiority trial, Community mental health

## Abstract

**Background:**

There is substantial evidence that cognitive therapy is an effective intervention for the treatment of major depressive disorder. Although dynamic psychotherapies have been widely studied and are commonly practiced worldwide, there are few randomized comparisons of cognitive therapy and dynamic therapy for major depressive disorder.

**Methods:**

We are completing data collection on a randomized non-inferiority trial comparing the effectiveness of cognitive therapy and short-term dynamic psychotherapy in the treatment of major depressive disorder in the community mental health setting. Therapists employed in the community setting have been recruited for training in either short-term dynamic psychotherapy or cognitive therapy. Patients seeking services at the community site who meet criteria for major depressive disorder based on a blind independent diagnostic interview are randomized to 16 sessions of treatment. All patients are assessed at baseline and months 1, 2, 4, and 5 utilizing a comprehensive battery.

**Discussion:**

This study adds to the growing literature evaluating the effectiveness of short-term dynamic psychotherapy for specific diagnostic groups. These results will have implications for the dissemination of effective interventions for major depressive disorder in community mental health settings.

**Trial registration:**

This trial is registered at ClinicalTrials.gov, a service of the United States National Institute of Health. NIH Identifier: NCT01207271. Registered 21 September 2010.

## Background

Major depressive disorder (MDD) is a severe and disabling disorder. Recent estimates of the worldwide prevalence (current and past month) of MDD is 4.4% (Ferrari et al. 2013). In the United States, approximately 17% of individuals have an MDD episode in their lifetime (Kessler et al. 2005). Data from the Global Burden of Disease study indicates that in the U.S. in 2010, MDD was the fifth ranked disease/injury in terms of disability adjusted life years (U.S. Burden of Disease Collaborators 2013). The pain and suffering of individuals with depression and those close to them result in a heavy economic toll to this country in terms of both treatment costs and lost productivity (Greenberg et al. 2003).

There is substantial evidence supporting the efficacy of cognitive therapy (CT; Beck et al. 1979) in the treatment of MDD. The effects of CT have been shown to be equal to well-conducted pharmacotherapy (Hollon et al. 1992; Murphy et al. 1984; Rush et al. 1977; DeRubeis et al. 2005). In addition, there is evidence that CT has a relapse prevention effect (Evans et al. 1992; Kovacs et al. 1981; Simons et al. 1986; Hollon et al. 1991; Hollon et al. 2005). In fact, Hollon et al. (2005) found that CT had a relapse prevention effect that lasted beyond the end of treatment and was as effective as keeping patients on continued antidepressant medication. Finally, benchmarking and effectiveness studies have demonstrated that CT is also effective in real-world practice settings (Persons et al. 1999; Merrill et al. 2003).

Dynamically oriented psychotherapies have been and remain widely practiced in the United States and continental Europe. An international study of over 4000 psychotherapists revealed that 35.8% reported their theoretical orientation as psychodynamic; only an “eclectic” orientation was more common (Heinonen & Orlinsky 2013). Similarly, among psychologists in the U.S., a psychodynamic approach continues to be the most prevalent single theoretical orientation (Norcross & Rogan 2013).

Despite the large numbers of practicing psychologists and psychiatrists using dynamic therapy worldwide, there are few high quality randomized effectiveness studies using adequate control conditions, standardized treatments, and well-specified patient populations. Although a number of studies of dynamic psychotherapy have been conducted and reviewed (Leichsenring et al. 2014; Abbass et al. 2014; Leichsenring & Klein 2014; Gerber et al. 2011; Driessen et al. 2010; Abbass & Driessen 2010; Shedler 2010; Connolly Gibbons et al. 2008; Fonagy et al. 2005; Leichsenring 2001), very few investigations to date have met the stringent criteria laid out by Chambless and Hollon (1998) that have become the gold standard for defining psychotherapies as evidence-based. Thus, dynamic therapy for MDD has been characterized as having only “modest” research support, while CT for MDD has “strong” research support (Society for Clinical Psychology, American Psychological Association, Division 12, 2014).

Despite the lack of comparative effectiveness trials comparing dynamic therapy to CT, there persists a sense that dynamic psychotherapy is inferior to CT. In fact, a recent meta-analysis (Marcus et al. 2014) of 51 psychotherapeutic investigations concludes that there is consistent evidence supporting the superiority of CT over dynamically oriented treatments. However, these conclusions are drawn from only 3 studies that directly compare dynamic therapy to CT. Giesen-Bloo et al. (2006) found a moderate effect at 3 years in favor of schema focused therapy over transference focused psychotherapy in the treatment of borderline personality disorder. Barkham et al. (1999) found no difference between 3 sessions of either CT and dynamic therapy in the treatment of subsyndromal depression. Finally, Watzke et al. (2012) report an advantage for inpatient CT over inpatient dynamic therapy using nonmanualized interventions across common mental disorders. Despite the broad conclusions of the meta-analytic review, these three investigations hardly warrant the conclusion that there is consistent evidence of the superiority of CT and provide no evidence to support the superiority of CT for MDD specifically.

In regard to MDD, evidence meeting the strict criteria outlined by Chambless and Hollon (1998) supporting the effectiveness of short-term dynamic psychotherapy is beginning to accumulate. Such evidence is critical to daily clinical decision making and contemporary public health policy, given that this treatment is so widely practiced. Two well-designed investigations indicate that short-term dynamic psychotherapy should be considered efficacious for MDD in the context of concurrent psychotropic medication usage. Both de Jonghe et al. (2001) and Burnand et al. (2002) compared combined dynamic psychotherapy plus antidepressant treatment to antidepressant treatment alone. Both of these investigations implemented manualized dynamic psychotherapies (16 sessions in the case of de Jonghe et al. and 10 weeks in the case of Burnand et al.), randomized patients to treatments, and otherwise used sound experimental methods. Both investigations showed that the combined short-term dynamic psychotherapy and medication interventions were statistically superior to medication alone in the treatment of MDD. These investigations do not provide us with information regarding the efficacy of short-term dynamic pychotherapy when implemented alone, but they do suggest that short-term dynamic psychotherapy for MDD is an effective treatment in the context of medication, a context that is quite common in current mental health treatment. Further, the Burnand et al. (2002) investigation implemented a supportive session with a nurse in the medication alone condition, indicating that the effects may be due to the specific interventions of the dynamic treatment rather than the non-specific relationship effects of a purely supportive intervention.

More recently, Driessen et al. (2013) have presented the best evidence to date indicating that short-term dynamic psychotherapy should be considered an evidence-based psychotherapy for MDD. The Driessen et al. (2013) study, conducted in outpatient clinics in the Netherlands, was a non-inferiority trial comparing CBT to psychodynamic psychotherapy for 341 patients suffering from MDD, making it the largest randomized trial of dynamic psychotherapy for MDD published to date. The results indicate that psychodynamic psychotherapy was not inferior to CT in the treatment of MDD on measures of depression severity. Although many have drawn the conclusion that interventions are equivalent when underpowered superiority tests have failed to demonstrate statistically significant differences, this study specifically demonstrated that dynamic psychotherapy was statistically significantly non-inferior to CT. Our protocol builds upon this accumulating evidence. We have conducted a randomized comparative effectiveness trial comparing CT to short-term dynamic psychotherapy in the treatment of MDD. Like Driessen et al. (2013), this trial was designed and powered to be a non-inferiority trial. Our protocol builds on the Driessen et al. (2013) study by extending outcome assessment beyond the measurement of depression severity to include assessment of changes in functioning and quality of life and by including blind independent ratings of treatment fidelity to validate that the treatments were implemented in accordance with the treatment manuals and to demonstrate that the treatments can be distinguished.

An important distinguishing feature of our trial is that it was conducted in a community mental health setting in the U.S. In 2008, over 17 million people utilized community mental health centers (CMHCs). Thirty-five percent of these individuals were insured through Medicaid and 38% were uninsured (Wells et al. 2010). Thus, CMHCs provide service to a large number of low-income individuals within the U.S. Compared to results from efficacy trials, the treatment of MDD within the CMHC setting is less successful. Response rates for pharmacological treatment of MDD in the public sector have been reported to be less than 30% (Rush et al. 2004). Effective ways of improving the treatment of those with depressive disorders in CMHCs are therefore sorely needed. Some data on the effectiveness of CT for MDD in a CMHC setting has emerged (Merrill et al. 2003), as well as a pilot study of psychodynamic therapy (Connolly Gibbons et al. 2012), but no studies comparing different psychotherapies in the CMHC setting have been conducted to date. The generalizability of the Driessen et al. (2013) study to a low-income U.S. CMHC population, which includes a substantial ethnic minority population, is uncertain. Efforts are currently underway to disseminate CT to CMHC settings in the U.S., and such training is costly (Creed et al. 2014). Thus, it is timely to investigate whether a commonly practiced treatment (psychodynamic therapy) is inferior to CT in the treatment of MDD in the CMHC setting.

By conducting our study in a CMHC setting, unlike many efficacy trials, this trial uses patients seeking treatment and therapists providing services in the community setting. As such, the study attempts to balance internal and external validity. Although our clinicians were real world clinicians working at the community mental health site, we implemented an intensive yet flexible training program at the site to standardize the treatment delivery and ensure treatment fidelity. In addition, we included patients seeking treatment at the center and implemented few exclusion criteria to ensure that the final sample represented those receiving services in the community. However, we implemented independent blind expert ratings of diagnosis and depressive symptoms to ensure that the patient sample was well-defined and that depressive symptomatology was reliably and validly assessed.

The primary hypothesis for this trial was that short-term dynamic psychotherapy would not be inferior to CT in change in depressive symptoms for patients with MDD receiving services in a community mental health setting. Our secondary hypothesis was that short-term dynamic psychotherapy would not be inferior to CT on secondary measures of patient-rated symptoms, functioning, and quality of life. We will also investigate the mechanisms of both CT and short-term dynamic therapy in the context of the randomized trial.

## Methods

### Design

This study is a longitudinal, randomized, non-inferiority trial being conducted in a large community mental health clinic. The objective of a non-inferiority trial is to show that the new or non-established treatment is not worse than the well-established treatment by more than a pre-specified *non-inferiority margin.* This non-inferiority margin was defined for the current trial as the difference between the treatment groups that would be considered the minimum clinically relevant difference. Though most comparative studies of psychotherapies historically have used samples of 30–50 participants per treatment group, non-inferiority studies typically require larger sample sizes to conclude that one treatment is not inferior to another within the pre-specified minimal clinically meaningful difference. The larger sample size of 237 randomized patients used in the current non-inferiority trial confers an advantage over previous superiority trials: in addition to testing for non-inferiority, a separate test is also possible for superiority, and the study was designed with adequate statistical power for both tests.

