### Study progress

This study began enrollment on October 10th, 2010 and the target enrollment of 237 patients was completed on July 2nd, 2014. This study was powered to randomize 230 patients to the two treatment condition, estimating that 203 patients would have at least one post baseline assessment. To date we have randomized 237 patients to the two treatments and have 208 patients with at least one post-baseline assessment. Recruitment for this protocol has closed with 7 patients still engaged in active treatment and 16 patients still due for follow-up assessments. Data collection is expected to be completed by December, 2014.

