#### Hypothesis 1: short-term dynamic psychotherapy will be not inferior to CT on change from baseline to endpoint of acute treatment in the HAM-D total score

This hypothesis is formulated in terms of a non-inferiority test, which is a one-sided equivalence test. The non-inferiority margin will be established to be smaller than any clinically relevant change and will be based on the recommendation for this provided by McHorney et al. (1994) and previously implemented in a non-inferiority study of treatments for MDD (Szegedi et al. 2005): a non-inferiority margin of 2.5 HAM-D total score points (this is the difference in change from baseline to endpoint between the two treatment groups). Standard deviation of change scores on the HAM-D are not typically reported in published studies, but standard deviations from two large studies of CT ranged from 6.4 (from Dimidjian et al. 2006) to 6.8 (DeRubeis et al. 2005). However, one published study of medication for MDD found a standard deviation of 8.5 (Szegedi et al. 2005). Although the studies with CT groups had lower standard deviations, these studies were not done in community settings where variability would be expected to be higher. Thus, to be conservative, we will use the higher figure (8.5) from the Szegedi et al. (2005) study. Based on the 8.5 standard deviation of HAM-D total score change scores, the 2.5 HAM-D points corresponds to a Cohen’s *d* effect size of 0.29.

We expect that some patients will fail to complete the study. We will implement pattern mixture models to assess the randomness of the “completion” process. If the process is random, we will implement the modified two one-sided test approach for equivalence discussed by Lee et al. (2005), who discussed a maximum likelihood statistical procedure for analyzing equivalence trials with missing observations.

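### The plan's own margin, SD and sample size give about 55–67% power for the primary non-inferiority test, so the claim of adequate power is not supported; for superiority no target effect is stated

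*Protocol article*

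**What the plan says.** All references are to the protocol article.

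- **Design:** having given the size as 237 randomised, the text says that "a separate test is also possible for superiority, and the study was designed with adequate statistical power for both tests". It attaches no power figure, alpha or superiority effect.
- **Hypothesis 1:** the primary test is one-sided, on change from baseline to the end of acute treatment, with "a non-inferiority margin of 2.5 HAM-D total score points". On variability, "standard deviations from two large studies of CT ranged from 6.4" to 6.8, but the plan expects more spread in community settings: "Thus, to be conservative, we will use the higher figure (8.5"), a value taken from a medication trial. It adds that "the 2.5 HAM-D points corresponds to a Cohen’s" d of 0.29.
- **Study progress:** "This study was powered to randomize 230 patients to the two treatment condition, estimating that 203 patients would have at least one post baseline assessment". The achieved figures are also given: "To date we have randomized 237 patients to the two treatments and have 208 patients with at least one post-baseline assessment".
- **Randomization:** allocation is 1:1.
- **Hypothesis 2:** the same d of 0.29 serves as the margin for the secondary measures.

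**The concern.** The article prints the margin, the SD, the allocation ratio, the planned numbers and the conclusion that power is adequate. Apart from alpha, nothing is missing that is needed to check the primary test. The conclusion does not follow from those inputs. This is therefore a stated property that fails its own check, not a detail left to a fuller document.

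Non-inferiority is the primary hypothesis. If the two therapies were truly identical, the design as described would still fail to show non-inferiority in about 33% to 45% of trials. A reader told that power was adequate could take such a failure as evidence against dynamic therapy, when it would be inconclusive.

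**Working it through.** **Inputs.** Margin 2.5 points and SD of change 8.5 (Hypothesis 1); 1:1 allocation (Randomization); 230 randomised and 203 evaluable planned, 237 and 208 achieved to date (Study progress). Assumed, because the article does not state them: one-sided alpha of 5% or 2.5%, true difference 0, and 80% as the usual minimum for adequate power. All figures use the normal approximation.

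**Figures that reproduce.** 2.5/8.5 = 0.294, the stated d of 0.29. The planned loss is (230 − 203)/230 = 11.7%.

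**Non-inferiority power, unadjusted change to endpoint.**

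SE = SD × √(4/N), and power = Φ(2.5/SE − z).

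For N = 203 and SD 8.5: SE = 8.5 × √(4/203) = 1.193, and 2.5/1.193 = 2.095.
- One-sided 5%: Φ(2.095 − 1.645) = 67.4%
- One-sided 2.5%: Φ(2.095 − 1.960) = 55.4%

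| N | SD | One-sided 5% | One-sided 2.5% |
|---|---|---|---|
| 203 (planned evaluable) | 8.5 | 67.4% | 55.4% |
| 208 (evaluable to date) | 8.5 | 68.3% | 56.4% |
| 230 (planned randomised) | 8.5 | 72.1% | 60.7% |
| 237 (all randomised) | 8.5 | 73.2% | 61.9% |
| 203 | 6.8 | 83.5% | 74.5% |
| 203 | 6.4 | 87.2% | 79.5% |

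At SD 8.5 and N = 203, even a one-sided alpha of 10% gives only 79.2%.

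**What an observed result would have to be.** At one-sided 2.5% the confidence interval half-width is 1.96 × 1.193 = 2.34, so the observed deficit may be at most 2.5 − 2.34 = 0.16 points. At one-sided 5% the limit is 2.5 − 1.645 × 1.193 = 0.54 points.

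**Size needed for 80% power.** n per arm = 2 × (z + 0.842)² × (SD/2.5)². To get the number randomised, divide the evaluable total by 203/230.
- SD 8.5, one-sided 5%: 143 per arm, 286 evaluable, about 325 randomised
- SD 8.5, one-sided 2.5%: 182 per arm, 364 evaluable, about 413 randomised
- SD 6.4, one-sided 2.5%: 103 per arm, 206 evaluable, about 234 randomised

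Only the last line lies near the stated 203 and 230. Read the other way, 203 evaluable patients give 80% power only if the SD is at most 7.16 (one-sided 5%) or 6.36 (one-sided 2.5%).

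**Superiority, two-sided 5%, N = 203, SD 8.5.** For a true difference of 2.5 points: Φ(2.095 − 1.960) = 55.4%. Difference detectable with 80% power: (1.960 + 0.842) × 1.193 = 3.3 points, or d = 0.39.

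**The case against.** **The analysis may be more efficient than an unadjusted comparison.** The plan names a maximum likelihood procedure for missing observations, allows covariates in its models, and describes a mixed model with baseline as covariate that averages the post-baseline visits. The gain depends on correlations that the article does not give. Assume equal correlations ρ of 0.3 to 0.7 and treat 8.5 as the change-score SD.
- Baseline adjustment of a single endpoint multiplies the variance by (1 + ρ)/2. With 203 patients, non-inferiority power becomes 83% to 73% at one-sided 5%, and 74% to 62% at one-sided 2.5%.
- Averaging four post-baseline visits with baseline as covariate multiplies the variance by [(1 + 3ρ)/4 − ρ²]/[2(1 − ρ)]. Power for 2.5 points at two-sided 5% becomes 98% to 86%.

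So a gain is possible, and the 55–67% belongs to the unadjusted endpoint comparison. But the averaging model is labelled secondary and addresses mean separation over treatment, whereas Hypothesis 1 is about change to endpoint. Adjusting the endpoint alone passes 80% only at one-sided 5% with a low correlation.

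**Alpha and target power may stand in the full protocol.** That is fair, and their absence here is not the complaint. Neither conventional alpha brings the unadjusted comparison to 80% at SD 8.5.

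**SD 8.5 is described as conservative.** At 6.4 to 6.8 power is about 84–87% (5%) or 75–79% (2.5%). This stands as a sensitivity result, but the plan gives a reason for not relying on those values.

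**The superiority claim has not been shown false.** This stands. A reader might infer that superiority power is 55%, but that figure assumes a true difference of exactly 2.5 points, and the plan names no superiority target. The Design section treats the margin as the smallest difference of clinical relevance, while Hypothesis 1 places it below any change that would matter clinically. On the second description a target above 2.5 points is consistent with the text.

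**Conclusion.** The point holds for the primary test. With margin 2.5, SD 8.5, 203 evaluable patients and no true difference, power for non-inferiority on unadjusted change to endpoint is about 67% (one-sided 5%) or 55% (one-sided 2.5%). It stays below 80% even with all 237 randomised (73% or 62%). The result rests on the assumed alpha levels and on an unadjusted comparison. The secondary measures carry the same standardised margin, so with similar numbers each would have about the same power.

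For superiority, the claim is unsupported by the stated inputs and no more than that: adequacy depends on a target effect that is not given, and 80% power starts at about 3.3 points.

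Two further inferences go beyond the documents. The near match with SD 6.4 (206 and 234 against 203 and 230) suggests where the size may have come from, but does not prove it; what is established is that the adopted SD and the planned size do not fit together. Nor does low power raise the risk of wrongly declaring non-inferiority. Its cost is a higher chance of an inconclusive trial.

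**What to change.** 1. Replace the adequacy sentence in the Design section with the one-sided alpha, the assumed SD and the resulting non-inferiority power: 67% (5%) or 55% (2.5%) at SD 8.5 with 203 evaluable. Add the sensitivity over SD 6.4 to 8.5, as tabulated above.
2. Reconcile the SD of 8.5 with the 230 randomised and 203 evaluable. If the size was derived from another SD, say so.
3. State the superiority effect the trial can detect, about 3.3 points (d = 0.39) for 80% power at SD 8.5. Use one description of how the 2.5-point margin relates to clinical relevance.
4. If a gain from baseline adjustment was assumed, state the correlation.
5. State in advance that failure to show non-inferiority is inconclusive and is not evidence of inferiority.

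The cost is rewording and one recalculated power statement. Recruitment has closed, and neither added enrolment nor a change of primary model is required. The downside is that the stated power becomes less favourable.
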